## Discussion

### Study management and safety

The University of Bath, as Sponsor, will be responsible for monitoring and auditing the study. The supervisory team will monitor the progress of the study and conduct audits to confirm appropriate data storage. The supervisors and the lead researcher will meet at the beginning, midpoint and end of the study to monitor data and adverse events, and to make recommendations regarding safety and ethical issues.

The safety and well-being of participants will be assured throughout the study. The environment and equipment are regularly examined for safety considerations. There is a small risk of falling if participants lose their balance when performing motor tasks, but the risk of falling is considered very low and is no greater than when performing these daily activities outside the laboratory. Gait retraining sessions require changes in gait patterns, which have a very small possibility of causing discomfort or a slight amount of pain during walking. If this happens, we will adjust the target gait patterns to reduce pain as soon as possible and if pain persists then the participant will be removed from the study.

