### Gait training sessions

From week one to week six, participants will attend weekly training sessions to perform constant preferred speed walking on the treadmill. The treadmill walking speed might be different from the preferred overground walking speed during assessment sessions, considering the familiarity and energy expenditure on the treadmill. The constant treadmill walking speed will be set to be 0.1 m/s slower than their choice of preferred speed on treadmill, considering the increased difficulty while interacting with feedback during gait retraining. Training time will gradually increase from 15 min in week 1 to 30 min in week 6 (Fig. 2). For the two intervention groups, real-time biofeedback graphs will be provided with personalised targets while walking on the treadmill. The feedback will be graphical data, not numerical data. The control group will perform treadmill walking for the same length of time without any feedback or instruction. The length of feedback time in the intervention groups will go up by the same amount (three minutes) per week until week 4, while it will remain the same (24 min) from week 5 onwards (Fig. 2).

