**Fig. 2 Fig2:**
[figure not shown]
Schedule of training time and feedback time during gait retraining sessions from week 1 to week 6. The orange line represents treadmill walking time, which is identical for all three group. The grey line represents feedback time, which is identical for the two intervention groups

For the participants in the two intervention groups, outside of the lab they will be asked to practice the new gait pattern at least 10 min per day, while also trying to maintain this pattern during the rest of their daily walking. All participants will be given a new weekly activity log and a physical activity monitor at the end of each training session.

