### Withdraw criteria

Participants will be informed that they are free to withdraw from the study prior to, during and after all data collection sessions. Once the data have been collected, access to change or remove a participant’s data will be limited, as we need to manage information in specific ways for the research to be reliable and accurate. If a participant withdraws from the study, we will keep the already obtained data.

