### Statistical analysis

Study outcomes will be assessed quantitatively. The primary outcome will be KAM and KAM impulse, while NRS pain and WOMAC scores will be considered secondary. All other biomechanical outcomes (e.g. spee, EMG data, gait pattern variables) will become exploratory outcome variables in nature. The primary success of the trial will be based on a comparison of KAM reduction between week 0 and week 6, while the success of retention will be based on a comparison of between week 0 and week 10. In the knee moment feedback group, gait pattern changes (FPA, step width and step length) from week 1 to week 6 and 1-month follow-up will be compared to explore the evolvement of the gait pattern in response to knee moment feedback intervention. The proportion of participants adequately completing the programme and the average number of training sessions completed will be reported.

All outcomes will be analysed using the intention-to-treat approach and thus we will include data from all enrolled participants, regardless of dropout. Descriptive statistics will be used to compare participants randomised into the two intervention groups and a control group with respect to baseline variables. Continuous variables will be expressed as the means and standard deviations (if normally distributed). The data normality and sphericity will be tested using Shapiro–Wilk test and Mauchly’s test respectively. Linear mixed effect (LME) models will be used to evaluate whether knee loading variables, knee pain score and WOMAC score significantly differ between the three time points (week 0, week 6 and week 10), with group as fixed effect, and participant (repeat measures) as a random effect. LME will be used for our primary objective to explore the difference between baseline assessment (week 0) and post-intervention assessment (week 6) with comparison of gait pattern group and control group, and the secondary objective to explore the gait pattern difference across all time points in knee moment group. The example LME formula for comparison between the gait pattern and control group within MATLAB is stated as below:$${\text{glme}}\_\mathrm{KAM }=\mathrm{ fitglme}({\text{data}},\mathrm{ ^{\prime}}{\text{KAM}}1 \sim \mathrm{ Group }+\mathrm{ timepoint }+\mathrm{ timepoint}*\mathrm{Group }+ (1|{\text{Participant}})\mathrm{^{\prime}},\mathrm{ ^{\prime}}\mathrm{FitMethod^{\prime}},\mathrm{^{\prime}}\mathrm{Laplace^{\prime}})$$

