Where KAM1 is the1st peak KAM; Group is the gait pattern group and control group; Timepoints includes baseline and post-training.

Repeated measures Bland–Altman analysis will be used to test the similarity between gait pattern group and knee moment group [35].

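### Persisting pain from retraining ends study participation rather than retraining alone, so week-6 outcomes can be lost for a pain-related reason in the feedback arms only

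*Protocol article*

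**What the plan says.** The rule is in Study management and safety. Retraining is described as requiring gait changes "which have a very small possibility of causing discomfort or a slight amount of pain during walking". If that happens, the target is adjusted, and "if pain persists then the participant will be removed from the study".

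Other sections bear on what follows from this:

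- **Withdraw criteria:** "If a participant withdraws from the study, we will keep the already obtained data". Nothing is said about collecting more.
- **Overview of the programme:** the post-training assessment is held at the end of the last training session in week 6. The week-10 retention assessment is for the two feedback groups only.
- **Gait training sessions:** "The control group will perform treadmill walking for the same length of time without any feedback or instruction". The feedback groups are also asked to practise the new pattern at home, "while also trying to maintain this pattern during the rest of their daily walking".
- **Qualitative assessment:** WOMAC and NRS pain are taken at the assessment sessions only.
- **Statistical analysis:** "NRS pain and WOMAC scores will be considered secondary". The approach is intention to treat, "thus we will include data from all enrolled participants, regardless of dropout". In the model shown for gait pattern versus control, "Timepoints includes baseline and post-training".

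**The concern.** Stopping a painful intervention and ending a participant's time in the trial are separate decisions, and the rule merges them. Safety requires only the first. The second discards outcome data that could still be collected.

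Two features make this loss more troublesome than ordinary dropout. It is one-sided by construction: the trigger (an altered gait) and the first remedy (a new target) do not exist for controls, who are offered retraining only after they finish at week 6. The reason for removal is also pain, close to what NRS and WOMAC measure. A mixed model handles missing week-6 values without bias only if the missingness can be explained by observed data. For these two outcomes, the only observed value for someone removed before week 6 is the baseline one, taken before retraining began.

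At stake is the pain comparison between gait pattern feedback and control. If those removed would have had worse week-6 pain, the comparison flatters feedback. If their pain settles once retraining stops, little or nothing is lost.

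**Working it through.** **Does the text produce the loss?** The removal rule ends study participation. The withdrawal section keeps past data only. The week-6 assessment is attached to a training session that a removed person no longer attends, and no section gives another route to it. Followed as written, the week-6 NRS, WOMAC and overground KAM values are not collected.

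**Is the loss avoidable?** WOMAC is a questionnaire given at the start of the assessment session, and the activities are done at preferred overground gait (Assessment sessions). Neither needs a training session. By week 6 the preferred gait may include the practised pattern, so the assessment is not necessarily free of it.

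**Inputs.** The protocol gives no figure for this rule. It does give planned arm sizes of 20 (gait pattern) and 10 (control) under Study population/sample size. The underlying 17 per group at an effect size of 1.01 reproduces: a two-sided t-test at 0.05 with 80% power gives 16.4, rounded up to 17. The following are assumptions:

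- k: number removed from the gait pattern arm before week 6 (1 or 2)
- d6, d0: how much worse the removed participants' pain is than that of those retained, at week 6 and at baseline, in SD
- rho: baseline to week-6 correlation (0.5, with 0.3 and 0.7 shown)

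**Formula.** The mean over all 20 at week 6 exceeds the retained participants' mean by (k/20) × d6. The model recovers from baseline only about (k/20) × rho × d0. The overstatement of pain benefit is therefore

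`bias = (k/20) × (d6 − rho × d0)`

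| Assumption | rho | k = 1 | k = 2 |
|---|---|---|---|
| No difference at either time | 0.5 | 0 | 0 |
| 1 SD worse at week 6 only | 0.5 | (1/20) × 1 = 0.05 | (2/20) × 1 = 0.10 |
| 1 SD worse at both times | 0.3 | (1/20) × 0.7 = 0.035 | 0.07 |
| 1 SD worse at both times | 0.5 | (1/20) × 0.5 = 0.025 | 0.05 |
| 1 SD worse at both times | 0.7 | (1/20) × 0.3 = 0.015 | 0.03 |
| 1 SD worse at baseline only | 0.5 | −0.025 | −0.05 |

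**Check by simulation.** The planned model form was simulated: group by time with a random intercept, maximum likelihood, 20 versus 10, two time points, 1000 runs per scenario, simulation error 0.001 to 0.002. At rho = 0.5, for k = 1 and 2 respectively, it gave:

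- worse at week 6 only: 0.050 and 0.104
- worse at both times: 0.026 and 0.045
- worse at baseline only: −0.026 and −0.052

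For worse at both times it gave 0.035 and 0.069 at rho = 0.3, and 0.015 and 0.030 at rho = 0.7. The formula is adequate.

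**Scale.** At rho = 0.5 the standard error of the group-by-time effect is sqrt((1/20 + 1/10) × 2 × (1 − 0.5)) = sqrt(0.15) = 0.387 SD. The largest bias in the table is 0.10/0.387 = 26% of one standard error.

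**Precision.** This is a lesser matter. At an effect size of 1.01, t-test power is 0.71 with 20 versus 10 and 0.69 with 18 versus 10.

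**The case against.** The strongest reply is that this hardly matters. The protocol expects such pain to be rare and slight. The identification session already looks for a pain-free pattern, from which the gait pattern arm's targets are taken, and target adjustment comes before removal. Pain provoked by an imposed gait would plausibly ease once that gait is dropped, which is the near-zero case above. Nothing in the document supports a persistent 1 SD deficit. All of this stands. It limits the size but does not restore the missing values.

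Other replies carry part of their weight:

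- **The two-time-point formula is given for KAM, while pain is to be modelled over weeks 0, 6 and 10.** True, but a person removed before week 6 also lacks week 10, so baseline is still all they contribute on pain.
- **Controls also have painful knees, walk on the treadmill weekly and may withdraw.** True. Pain-related loss overall need not be one-sided; what is one-sided is the loss that this rule imposes.
- **There is a 20% dropout allowance, and programme completion will be reported.** The allowance addresses precision, not selection. Reporting completion makes removals partly visible but recovers no data.
- **Intention to treat is promised.** The removal rule does not literally contradict that statement, but analysing everyone as randomised cannot supply values never collected.
- **An article condenses the full protocol.** Follow-up after stopping treatment is often left to the full document. Here, however, the article states affirmatively that the person leaves the study, and staff could follow it as written.

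**Conclusion.** The concern holds, as a minor point. As written, the rule can remove week-6 NRS, WOMAC and KAM values for a pain-related reason, in the feedback arms only.

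Each removal costs 5% of the gait pattern arm's week-6 data. With one or two removals, the pain benefit is overstated by between 0 and 0.05 SD or between 0 and 0.10 SD if those removed are no different at baseline and up to 1 SD worse at week 6. The upper ends halve if they were equally worse at baseline (correlation 0.5), and the sign reverses if they were worse at baseline only. The removal rate, the pain of those removed and the correlation are all assumed. The conclusion concerns secondary outcomes; nothing is claimed about bias in KAM or about the primary success criterion. The case for change rests on how little it costs, not on a large expected bias.

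**What to change.** Replace the removal sentence in Study management and safety with wording to this effect: if pain persists after the target has been adjusted, retraining is stopped; the participant, if willing, stays in the study and attends the planned week-6 and week-10 assessments without a training session, giving WOMAC and NRS, and KAM at preferred overground gait if able. Add that such participants are analysed as randomised and that the reason for stopping is recorded by arm. The decision to stop retraining remains a safety decision.

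The text change is one sentence. Because registration was retrospective and the trial was probably already running, it may also need an approved amendment and matching information-sheet wording. For participants, the cost is one or two visits already in the schedule, for a few people, with painful tasks skipped.

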### Data management and confidentiality

The University of Bath will act as the Data Controller for this study. Only the researcher team members will have access to the data. Personal information will never be identifiable in published papers or conference presentations. Data and participants information will be collected in accordance with the confidentially NHS Code of Practice and all information will be subject to the current conditions of the Data Protection Act. Each participant will be assigned a unique project code which will be used to identify the participant anonymously. An Excel data sheet maintained on a University X: Drive (password protected) will be used to record participant information. Signed consent form will be stored in a locked cupboard and kept for 10 years to evidence the consent process.

### Post-trial care

By identifying and practicing the optimal gait pattern identified in this trial, it is hoped that there will be physical benefits such as pain reduction, reduced knee loading, improved quality of life and reduced disease progression. Participants will be encouraged to keep practicing the gait pattern after they finish the study.

### Dissemination

The results of this study will be submitted for journal publications and conference presentations, which will be exposed to researchers and clinicians in the same field. We will also promote the study outcomes to a wider audience such as physiotherapists and individuals with KOA through internet media.

## Conclusion

To the best of our knowledge, this is the first study to explore the effectiveness of gait pattern biofeedback gait retraining on knee loading and knee pain in KOA population, compared to a control group. The results of this study will also identify the number of sessions needed to identify the optimal gait pattern using knee moment feedback. The similarity of effectiveness between gait pattern and knee moment feedback will be assessed as exploratory objective. The results can provide guidance of clinical implementation and further progress the development of portable gait retraining devices for use outside of the laboratory. This study will also explore the muscle activation alterations during gait retraining sessions, which can help illuminate the potential effective mechanisms of gait retraining. Furthermore, this study aims to close the knowledge gap in the literature on the translative effect of gait retraining on other daily activities, such as stair climbing and sit-to-stand. A comprehensive and effective gait retraining programme may represent a practical and self-administered approach to slow KOA progression and improve quality of life in patients with knee osteoarthritis.

## Data Availability

Not applicable.

## Abbreviations

BMI: Body mass index
CSEOR: Centre for Sport Exercise and Osteoarthritis Research
EMG: Electromyography
FPA: Foot progression angle
KAM: Knee adduction moment
KFM: Knee flexion moment
KOA: Knee osteoarthritis
LME: Linear mixed effect
MVC: Maximum voluntary contraction
NRS: Numeric Rating Scale
PPI: Patient and Public Involvement
WOMAC: Western Ontario and McMaster Universities Arthritis Index
